### Data collection

Data variables collected pre-intervention or on day 0 will include baseline demographics, pain scores, EQ5D-5L (Quality of Life Questionnaire), and a number of key confounders that have been reported in the literature, and linked to long-term opioid use:

Baseline demographics (age, sex, body mass index (BMI), ethnicity, social deprivation scores, smoking and alcohol consumption).Surgical history (surgery type, hospital, ward, opioid – type, strength, duration, average pain score).Medical history (prior opioid use, prior gabapentinoid and psychotropic use, other medication use, comorbidities, healthcare use).

At each additional follow-up appointment data variables collected will include pain scores, further medication changes, symptom management and for final appointments only, EQ5D-5L and Participant Feedback Questionnaire data. The aim of this questionnaire is to ascertain their experience of the deprescribing intervention, their views, and opinions on the process. In addition, all participants will be invited to take part in an online or telephone interview after their final follow-up with the pharmacist.

### Data confidentiality

All data recorded from participants will be de-identified to the research study team in line with NHS governance (Unique Reference Number (URN) and date of birth) and transmitted to a secure server which is confidentiality/privacy standard compliant. Access to the de-identified data will be accessible via a password-protected website, by authorised members of the research team. All participants in the study will be assigned a URN at the first MUR with the clinical pharmacist. This URN which will consist of GP practice initials followed by sequential number (double digits) and their date of birth will act as a medical identifier for each participant. All data collected from participants will be de-identified to the research study team using the URN.

### Data management

Submitted data will be collected, reviewed for completeness, analysed, and stored in compliance with the Data Protection Act of 2018
^
47
^ by the University of Kent (UoK) research team members and public contributors where appropriate. All data will be entered onto a secure, database and accessible only to authorised members of the team. All participants recorded details will be anonymised and de-identified to the university’s research team by means of a unique research number, allocated during participant consent, by the clinical pharmacist. The handling of personal information by the research team will be clearly stated in the participant information sheet. All saved electronic data will be stored on password protected computers/laptops for a maximum of 5 years, post-project publication. All paper documentation, participant questionnaires, demographics data etc. will be stored in locked filing cabinets at the UoK (Medway School of Pharmacy). Paper documentation will be destroyed (shredded) five years post project publication. Similarly, all recorded interviews and transcripts will be deleted 5 years post-publication. Identifiable data (e.g., consent form) will be stored on secure UoK networks and destroyed 3 – 6 months after the study has ended.

### Statistical analysis

For the quantitative measures descriptive statistics will be used to describe the intervention population including patient demographic variables, deprivation scores, comorbidities for each surgical type, medication prescribed (including type, dose, amount, duration and long or short-acting), pain scores and history of opioid use. Descriptive statistics will also be used to assess de-escalation success rates, proportion of long-term users and quality of life. Similarly, descriptive statistics will be used to determine attrition rates at various stages and the different reasons provided. Means difference analyses will be performed via corrected repeated measures
*t*-test/Wilcoxon’s tests or mixed ANOVAs (depending on data distribution and number of participants) to test the difference of MME taken at discharge and 91-days post discharge in each of the three pathways. The allocation to pathway C or not will be treated as a dichotomous outcome variable in a set of logistic regression models to determine the significance of a number of predictors as risk factors. Chi-square analyses will be used to compare the proportion of patients who accepted or declined the intervention. For the health economic analysis, a micro-costing approach will be used to estimate the intervention costs, opioid and other analgesic medication costs, and relevant participant health resource use. The qualitative data from the interviews will be transcribed verbatim, entered into qualitative data analysis software (
NVivo v11) or Microsoft Excel 2021 and subjected to thematic analysis
^
48
^. Notes collected at each medication assessment meeting will be reviewed and analyses for themes related to recommendations for the intervention and the role of clinical pharmacists in deprescribing opioids post-surgery.

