### Aims and objectives

The primary aim of this study is to evaluate a multi-centre, pharmacist-led, early opioid deprescribing intervention. This is designed for patients discharged following a surgical procedure with an opioid prescription from hospitals within a single NHS Trust in an area of high opioid prescribing, East Kent. It will determine whether this designed intervention is able to support early deprescribing of opioids in this particular healthcare setting and with this particular patient population and to inform a much larger, clinical trial. A summary of the aims and objectives for this study are collated in
Table 1.

**Table 1. T1:** Summary of study aims and objectives.

Aims/questions	Objectives
**To test the feasibility of delivering an early opioid ** **deprescribing intervention in primary care, led by ** **trained clinical pharmacists.**	**Ascertain stakeholder acceptability of the intervention:** • Maintain detailed records of any barriers or enablers that may occur in response to setting up the intervention and whilst delivering the intervention • Deliver stakeholder interviews
	**Measure the capabilities of trained clinical pharmacists to deliver an ** **early opioid medication review by**: • Completed intervention delivery training • Observational competency checks by Clinical Lead • Completed medication review case reports • Number of participants successfully deescalated
	**Ascertain participant acceptability of the intervention by measuring**: • Number of participants that enrol in the study • Number of withdrawals from the study • Adherence to pharmacist medication recommendations • Responses to participant satisfaction questionnaire • Responses during participant interviews
	**Apply a micro-costing approach to estimate the intervention costs:** • opioid medication costs • staff costs • Health resource use (primary care services, community-based services, hospital inpatient and outpatient services)
**To measure successful discontinuation and/or ** **reduction in the use of opioids to within the ** **recommended 2–4-week period for opioid use ** **or by the expected period of tissue healing (<91 ** **days) whichever is sooner ^ 39 ^.**	**Measurement of** the mean difference in morphine milligram equivalent (MME) dose at baseline and at 90 days

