### Recruitment

**Participants**: Participants identified as having had surgery and discharged with opioids (<120 mg) within the last 7 days via participating GP practice sites undertaking weekly database searches and/or by screening discharge letters will be contacted by either an email or text, inviting them to participate in the study and providing a link to the patient information leaflet (PIL). Invited participants will then be contacted by the practice using a consecutive sampling approach via telephone within 48 hours of the invite being sent, asking if they would like to take part in the study, answering any questions and confirming their eligibility. For patients that agree to participate, an MUR appointment (online, telephone or in person) will be arranged with the pharmacist and a link to an online consent form sent to the participate to complete.

**Sample size:** A sample size of 80 – 100 participants will be recruited. Statistically, sensitivity power analyses have confirmed that the proposed number is able to detect significant differences of the expected effect size and is in line with the recommended sample size of 70 to estimate key parameters, bench-marked from external pilot randomised controlled trials
^
40
^ and will allow for participant loss, to follow-up.

**GP practices:** By utilising networks locally an Expressions of Interest document was circulated to GP practices in Kent. Further to this, research active practices in East Kent and South Kent were approached directly and capacity and capability assessed. Moreover, the project’s Clinical Lead contacted clinical pharmacists who had interest in, or experience in research of opioids or pain, to invite them to express interest in recruiting via their practice(s).

**Clinical pharmacists:** GP practice-based clinical pharmacists with experience of delivering MURs and opioid deprescribing will be recruited from participating practices. The clinical pharmacist/s will receive detailed information about the study, undergo some training with the study Clinical Lead and will be asked to provide written informed consent.

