### Outcomes measures

The primary outcome of the DESCALE study are to determine the feasibility of the designed intervention to support early deprescribing of opioids in this particular healthcare setting, using this particular healthcare personal and with this particular patient population, in order to inform a much larger, clinical trial. A summary of the study outcomes are listed in
Table 3.

**Table 3. T3:** Summary of outcome measures.

	Outcome Measure(s)
1	**Determination of** the fidelity of an early opioid deprescribing intervention led by trained clinical pharmacists in primary care and their role in the wider medicine’s optimisation programme
2	**Determination of** the barriers/enablers that affect the delivery of the intervention from the perspective of the NHS stakeholders
3	**Determination of** the barriers/enablers that affect the delivery of the intervention from the perspective of the surgical patient
4	**Establishment of** the cost of delivering the intervention from the health/social care provider (NHS), perspective
5	**Determination of** the percentage of participants that reduce or stop opioids within 91 days
6	**An understanding of** trends in surgical opioid prescribing, surgical related pain, and risk factors that contribute to long term opioid use
7	**Determination of** the integrity, robustness, and transferability of the protocol for future adoption by the NHS

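### The two-point MME comparison uses only participants with both doses, so it drops those lost before 91 days and leaves their Day 14 and Day 31 doses unused

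*Protocol article*

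**What the plan says.** Under Statistical analysis, the change in MME has a named method: "Means difference analyses will be performed via corrected repeated measures" t-tests or Wilcoxon tests, or mixed ANOVAs, depending on distribution and numbers. The time points are discharge and 91 days after discharge, and the comparison is made in each of the three pathways. Table 1 (Aims and objectives) has the same two-point form, with baseline and 90 days.

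Loss is foreseen. Recruitment states "A sample size of 80 – 100 participants will be recruited", describes this as "in line with the recommended sample size of 70 to estimate key parameters", and adds that the number "will allow for participant loss, to follow-up". Table 1 lists "Number of withdrawals from the study" as an acceptability measure, and attrition by stage, with reasons, is to be described.

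Intermediate data are planned. Table 1 has medication use collected at baseline and at every follow-up appointment, and Table 2 schedules follow-up at Day 14, Day 31 and Month 3. Table 2 and End of intervention let a participant finish early once opioids are discontinued.

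De-escalation success is a separate item. Table 3, row 5, defines it as "the percentage of participants that reduce or stop opioids within 91 days", and its analysis is descriptive: "Descriptive statistics will also be used to assess de-escalation success rates, proportion of long-term users and quality of life".

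**The concern.** A paired t-test or a Wilcoxon signed-rank test works on within-person differences, and a conventional mixed ANOVA on two time points excludes anyone with a missing cell. The chosen methods therefore decide who is in the MME estimate: those with a dose at both ends. A participant who leaves after the Day 31 visit contributes nothing, although the dose trajectory up to then is on file.

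This matters because continuing in a deprescribing study may be linked to how deprescribing is going. If it is, the mean fall among complete pairs is not the mean fall among those who entered. The MME change is the measure set against one of the aims in Table 1, and the study exists to inform a larger trial. Testing within pathways makes the groups smaller, so a few losses can shift a result.

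**Working it through.** **The plan's own figures.** Recruitment is 80 to 100 and the benchmark is 70. No loss rate is given. The power statement ("sensitivity power analyses have confirmed that the proposed number is able to detect significant differences of the expected effect size") cannot be reproduced, because the article gives no alpha, power, effect size or standard deviation. I do not count that as a fault in a condensed article.

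**Loss the plan could absorb.** (N − 70)/N gives:
- N = 80: 10/80 = 12.5%
- N = 100: 30/100 = 30%

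Check: 70/(1 − 0.125) = 80 and 70/(1 − 0.30) = 100. These are the most that could be lost with 70 still remaining. They are assumptions here, not rates the protocol expects.

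**What complete pairs discard.** Each lost participant can have up to two follow-up visits before Month 3. That is at most 10 × 2 = 20 unused follow-up doses at N = 80, or 30 × 2 = 60 at N = 100. It assumes that MME can be computed from the follow-up medication data. The article lists the MME calculation explicitly only for the baseline form.

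**Effect on the mean change.** Let p be the share lost, C the mean fall in complete pairs and L the mean fall in those lost. The all-participant mean is (1 − p)C + pL, so the complete-pair mean differs from it by p(C − L).
- p = 0.125: 12.5% of the gap between the groups
- p = 0.30: 30% of the gap

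If those lost had no fall at all (L = 0), C overstates the all-participant mean by a factor of 1/(1 − p), which is 1.14 or 1.43. If those without a 91-day value include many early stoppers, whose dose fell to zero, then L may exceed C and the sign reverses. The documents do not settle which applies.

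**Precision is the smaller issue.** Assuming two-sided alpha 0.05, 80% power and pooled pathways, the detectable standardised paired difference is 0.34 at n = 70, 0.32 at n = 80 and 0.28 at n = 100. Each per-pathway test would have fewer participants.

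**Supporting illustration for Table 3, row 5.** Assume 70 participants with known status, and all others unknown. The lower bound is s/N and the upper bound is (s + N − 70)/N, where s is the number of observed successes.

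| Observed success (Wilson 95% CI) | N = 80 | N = 100 |
|---|---|---|
| 56/70 = 80% (69.2–87.7%) | 56/80 = 70.0% to 66/80 = 82.5% | 56% to 86% |
| 63/70 = 90% (80.8–95.1%) | 63/80 = 78.8% to 73/80 = 91.3% | 63% to 93% |

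The worst case lies below the confidence interval in three of the four cells. At N = 80 with 56/70 it lies just inside (70.0% against 69.2%).

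**The case against.** Much of the opposing case stands, and it limits the point to the MME comparison.

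- A reader might infer that de-escalation success is estimated in completers only. The documents do not say so. The paired tests and ANOVA apply to MME; success is a separate descriptive percentage of participants. Its denominator is open in the article and may be fixed in the full protocol or the analysis plan, neither of which is shown, so its absence here is not a fault.
- A reader might take 12.5–30% as the protocol's expected attrition. It is only the loss that would still leave 70.
- A reader might infer that lost participants cannot be scored. The outcome is reduction or stopping within a 91-day window, so a reduction recorded at Day 14 or Day 31 already counts. Pharmacists also have access to practice records (Pharmacists and opioid management; GP notification and medication change recommendations), although using them to classify lost participants is neither stated nor excluded.
- A reader might assume that loss flatters the result. Pathway C does include patients unwilling to stop, which makes selective loss plausible, but nothing documents it, and early stoppers can push the other way.

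It is also fair to say that this is a non-randomised feasibility study, that attrition will be reported, and that the article itself concedes that its size limits confidence. This lowers the stakes. It does not remove the point that a named method sets aside data the study plans to collect, when a method that uses them is readily available.

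**Conclusion.** The point holds for the MME comparison. The stated two-point methods, as conventionally run, restrict the estimate to complete pairs unless values are filled in. The possible distortion is p(C − L), of unknown direction; p is at most 12.5% or 30% if 70 participants remain, and larger if fewer do. It would vanish if nobody were lost, or if those lost had the same mean change as those retained. The article does not show that bias will occur, and it does not show that the success percentage is wrongly defined. The bounds for Table 3, row 5 show only how wide the uncertainty could be under assumed losses and assumed success rates. This is a modest, inexpensive improvement to a stated analysis.

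**What to change.** In Statistical analysis, make the main MME analysis a repeated-measures mixed model using every recorded MME (discharge or baseline, Day 14, Day 31, Month 3), so that participants with partial follow-up contribute. Use a robust or bootstrap interval if MME is skewed. State how a participant who has stopped opioids and finished early is entered at later time points. Report the complete-pair result beside the model.

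As a supporting sensitivity analysis for Table 3, row 5, give the reduce-or-stop percentage over all participants who had the baseline medicines use review. Count any reduction or stop recorded before loss as observed, and show worst-case and best-case bounds for those whose status is truly unknown. If the full protocol or analysis plan already fixes this, a cross-reference is enough.

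Cost: revised wording and a little more analysis, with no new visits, provided follow-up medication data are complete enough to compute MME. The model relies on data being missing at random, which cannot be verified, and the reported figures may look less favourable.

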### Surgical opioid use

Opioids are routinely used pre-, intra-, and post-surgically for the treatment of acute pain and post-operatively for pain management and is a primary route to exposure to these types of medicines, often for the first time
^
14,
15
^. Evidence from the US and Canada has shown a clear link between post-surgical opioid prescribing for both minor and major surgery, and persistent long-term use in the community, beyond tissue healing. Inappropriate prescribing of opioids both peri- and post-operatively, accounts for 36.5% of all opioid prescribing in the US, with 3 – 10% of these patients transitioning to long-term use
^
11,
14,
16,
17
^. Patients undergoing surgery are almost four times more likely to be discharged with opioids than their non-surgical counterparts
^
18
^. This is often with more opioid medication than is actually required to treat post-surgical pain
^
19–
22
^. Perhaps more alarmingly, almost half (45%) of these patients are given opioids even though they would not have been taking any opioids at point of discharge
^
23
^. In the United States (US), a study showed that between 5.9 – 6.5% of all patients who underwent surgery (versus 0.4% of the non-surgical control) went on to become long-term opioid dependent, even if they had never taken opioids before
^
15
^.

It is becoming clear from the US, that postsurgical prescribing of opioids is a problematic, underexplored, new source of long-term opioid use
^
17
^. Compared to the US and Canada, less is known in the UK about peri-operative opioid prescribing in hospitals and any link to long-term use. Two recent studies in the UK have identified long-term opioid use (>1 year) to be associated with older age (>75 years), being socioeconomically disadvantaged, having a history of depression and/or alcoholism, prior gapapentinoid or psychotrophic use, and those initiated on >120 morphine milligram equivalents (MME) following major surgery
^
6,
24
^. There are over 5.6 million opioid prescriptions dispensed each year in the UK, corresponding to around 13% of the adult UK population
^
25
^ and over 4.7 million surgical procedures occurring each year
^
26
^ and nearly 8 million people on surgical waiting lists, with over 300,000 waiting more than 52 weeks for surgery
^
27
^. This, along with no current national guidelines on peri-operative opioid prescribing, a declining GP workforce and increasing patient numbers
^
28

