**To understand post-surgical opioid prescribing ** **experiences including opioid use, long-term ** **opioid use, participant pain and quality of ** **life in the 3-month period post-surgery when ** **discharged with an opioid prescription**	• Collect medication use data at baseline and at all follow-up appointments • Compare opioid prescribing (type, dose, amount) at baseline for each surgical speciality and hospital • Measure pain scores at baseline and final visits • Measurement of risk factors in the participant population that have been previously linked to long-term opioid use ○ Baseline demographics; ○ Medical, prescription and surgical histories. • Response to Quality-Of-Life questionnaire (EQ5D-5L) complete at baseline and final appointment • Responses during participant interviews
**To ascertain the feasibility of delivering the ** **intervention as per the protocol to inform a ** **future study or adoption of the protocol**	**Measurements of:** • Time spent finding and recruiting participants • Number of possible surgical participants per week that could receive intervention • Number of pharmacists available to deliver the intervention • Number of surgical participants that accept an early MUR versus the number that are asked • Time taken from hospital discharge to receiving first MUR. • Average time taken for each appointment • Average time taken to successfully deescalate opioids in surgical patients • Number of participants that are successfully deprescribed opioids within 3 months • Number of patients that require additional appointments with the pharmacist • Number of participants that require additional support post-90 days • Responses during participant interviews

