### Pathway B – Gradual de-escalation of opioids

For this pathway the clinical pharmacist may recommend ‘gradual’ discontinuation of opioids if any of the following apply:

➢Patient has been taking opioids for more than 7 days and/or the combined MME is more than > 30 mg – 120 mg/day or ≥12 µg/hr transdermal Fentanyl patches or ≥15 microgram (mcg)/hr Buprenorphine patches➢The medication is not providing useful pain relief and function has not improved➢Patient was taking opioids prior to surgery to treat pain related to their condition.➢Presents with other co-morbidities including mental health disorders➢Patient has a history of alcohol or substance abuse➢Patient is taking other medications (e.g., benzodiazepines, gabapentin, pregabalin or muscle relaxants) or medical conditions (lung disease, sleep apnoea, liver disease, kidney disease, fall risk, advanced age) that could increase the risk of adverse events (AEs)➢Patient requests a dosage reduction of their opioids➢The pharmacist feels it is safer to start with a gradual de-escalation of opioids

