### Pathway C – Continuation of opioids

In some instances, the clinical pharmacist will recommend that the patient should continue taking their prescribed opioids, which is reviewed again after one week, if:

➢Benefits of taking opioids outweigh the risk of discontinuing opioid therapy➢Prior opioid use was for another condition not related to the surgical procedure➢Patient does not want to discontinue their opioids

Pathway’s will not be exclusive to allow for patient variability in opioid withdrawal coping, and ongoing pain management and thus possible that patients will transition between pathway A and B, and from pathway C to B or A. We anticipate that for most participants, where opioids are being used primarily for the treatment of post-surgical pain or acute injury, pain which should normally subside after 3 – 4 days, and receiving opioids for the first time, will not require complex de-escalation protocols and psychological support. For those participants who have required prior (≤90 days) opioid use to manage their condition prior to surgery, or opioids for an unrelated condition, or on a higher dose, a more gradual discontinuation of opioids or referral to a specialist pain service, may be required.

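### The risk-factor regression models allocation to pathway C, a provisional care decision that partly overlaps with the predictors, not the long-term opioid use the study wants to explain

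*Protocol article*

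**What the plan says.** The Statistical analysis section names one regression for risk factors: "The allocation to pathway C or not will be treated as a dichotomous outcome variable in a set of logistic regression models", and gives its purpose as "to determine the significance of a number of predictors as risk factors". That sentence does not say what the factors are risks for. Other sections do:

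- Outcomes measures, Table 3, item 6 refers to "risk factors that contribute to long term opioid use".
- Aims and objectives, Table 1 lists "Measurement of risk factors in the participant population that have been previously linked to long-term opioid use".
- Data collection says the baseline variables were chosen because the literature links them to long-term use.

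The pharmacist and patient settle the pathway together after the review (Study MUR and biopsychosocial assessment protocol). Pathway C means opioids continue and are looked at again a week later, and it is "thus possible that patients will transition between pathway A and B, and from pathway C to B or A". The End of intervention section separately identifies participants who still take opioids at 91 days, but the Statistical analysis section gives the proportion of long-term users a descriptive summary only.

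**The concern.** The modelled event is not the event of interest. A pathway C patient may stop opioids well before day 91. A pathway B patient may still be taking them at day 91 and is nevertheless coded as a non-event.

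The event is also partly defined by the predictors. One pathway C criterion is "Prior opioid use was for another condition not related to the surgical procedure", and prior opioid use is among the variables to be collected. In the other direction, the Introduction cites UK studies that link long-term use to older age and to "having a history of depression and/or alcoholism, prior gapapentinoid or psychotrophic use". The pathway B list contains close counterparts: mental health disorders, a history of alcohol or substance abuse, advanced age, and "Patient is taking other medications (e.g., benzodiazepines, gabapentin, pregabalin or muscle relaxants". Patients moved to B for these reasons enter the model as not C.

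The study exists to inform a larger trial. If these coefficients were read as evidence on persistent use, a factor could be reported as unimportant or even protective because of how the pathways are assigned.

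**Working it through.** The protocol gives no figure for this regression, so there is none to reproduce. Two checks apply.

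**1. Can the choice of outcome distort a risk factor?** Consider a risk factor R that is also a pathway B criterion. All four inputs below are assumptions, because the protocol gives no expected pathway shares.

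- c0 = probability of pathway C without R = 0.20.
- m = how many times more likely patients with R would be to enter C if the B criteria had no effect = 1.5.
- s = share of would-be-C patients with R who are placed in B instead, varied from 0 to 90%.
- Use at 91 days: 5% without R and 12% with R, so the true odds ratio is (0.12/0.88)/(0.05/0.95) = 2.59.

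Odds ratio for pathway C = odds(c0 × m × (1 − s)) / odds(c0), where odds(p) = p/(1 − p) and odds(0.20) = 0.25.

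| s | P(C) with R | Odds ratio for C |
|---|---|---|
| 0% | 0.300 | 1.71 |
| 25% | 0.225 | 1.16 |
| 50% | 0.150 | 0.71 |
| 75% | 0.075 | 0.32 |
| 90% | 0.030 | 0.12 |

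At s = 75% the arithmetic is (0.075/0.925)/0.25 = 0.32. A simulation of 400,000 patients fitted by logistic regression gave 0.32 for pathway C and 2.57 for 91-day use. With c0 at 0.10 or 0.30 instead, the s = 75% result is 0.35 or 0.30.

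The sign reverses when m × (1 − s) < 1, that is when s > 1 − 1/m. The threshold is any redirection at all if m = 1, above 33% if m = 1.5, and above 50% if m = 2. Below the threshold the odds ratio is pulled down but keeps its direction.

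**2. How many events would the matching outcome give?** Expected events = N × rate, with N = 80–100 (Recruitment, Sample size) and the US rates cited under Surgical opioid use.

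| Rate | N = 80 | N = 100 |
|---|---|---|
| 3% | 2.4 | 3.0 |
| 5.9% | 4.7 | 5.9 |
| 6.5% | 5.2 | 6.5 |
| 10% | 8.0 | 10.0 |

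At 5.9–6.5%, the binomial probability of reaching even 10 events is 0.02–0.03 with 80 participants and 0.07–0.12 with 100. Its highest value, at 10% and N = 100, is 0.55. Correcting the outcome therefore does not make a set of logistic models supportable.

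**The case against.** The strongest reply is that the target is inferred. The regression sentence speaks only of risk factors, and long-term use is handled elsewhere by description. Strengths and limitations of this study also mentions finding people who need more support with deprescribing, and staying on opioids at review is a reasonable outcome for that aim. On this view the fault is one of labelling. This stands in part: the model can describe who is kept on opioids at review. But the protocol ties its risk factors to long-term use in three places, names no other regression for them, and nowhere equates pathway C with long-term use.

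Three stronger readings are tempting and are not supported:

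- *The signs will reverse.* Pathway B is something the pharmacist may recommend if any of its criteria applies. A patient with depression who does not wish to stop also meets a pathway C criterion, and the Figure 2 legend says the pathways are guidelines open to adjustment. The share redirected is unknown, so reversal is only a possibility.
- *The model is wholly circular.* Sex, BMI, ethnicity, deprivation and smoking are criteria for no pathway. For pathway C itself, literal overlap is shown only for prior opioid use.
- *Allocation is a baseline variable.* Table 2 lists pathway agreement at every visit, and the analysis section does not say which visit counts. The transitions described include none into C, which makes the first review the likely point of entry, but this is inference.

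Multiple testing and sparse events are separate matters. The number of predictors tested is not stated, and the protocol already concedes that the sample is small.

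**Conclusion.** The point holds in a limited form. Followed as written, the regression answers who is placed in pathway C, while the stated interest is who goes on to long-term use. The mismatch follows from the protocol's own sections and needs no assumption beyond reading the regression as serving outcome 6. A larger sample would not remove it.

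The size of the distortion cannot be fixed from the document. Under the assumed inputs the odds ratio for C runs from 1.71 with no redirection to 0.12 with 90% redirected, against an assumed true value of 2.59 for 91-day use. The 0.32 at 75% is an illustration, not a forecast.

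The 2–10 expected events rest on US rates that may not carry over to East Kent or to a definition at 91 days.

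This is a should-fix. The primary outcome is feasibility, the regression is secondary, and nothing in the protocol says its coefficients will set eligibility or targeting in the next trial.

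**What to change.** Change the Statistical analysis section as follows.

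- Make still taking any opioid at 91 days after discharge (yes/no) the outcome of the risk-factor analysis.
- Report the listed risk factors descriptively against it, with 95% confidence intervals.
- Limit any formal estimate to one predictor named in advance and labelled exploratory.
- Delete the aim of determining significance.
- Keep pathway allocation as a process measure of who continues opioids at review, and state which visit's allocation is used.

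The cost is mainly wording. Opioid status at 91 days is already needed for outcome 5, and the dose comparison already uses that time point. Because the intervention ends when opioids stop, the text should say how 91-day status is established for those who finish early. The downside is fewer and wider estimates. The pathway criteria themselves need no change for this purpose.
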